**Fig. 1 Fig1:**
[figure not shown]
Timeline of data collection. Note: MR = medical rehabilitation; IG = intervention group; CG = control group; GPs = general practitioners. Interviews with patients or GPs (study phase 1) are not shown

The SPIRIT flow diagram in additional file 3 summarizes the timeline for enrolment, interventions and assessments.

### Randomization

Using a two-period cluster randomized crossover design, study participants (rehabilitation patients) will be randomized at the facility level: during the first nine months of data collection, the intervention will be carried out in half of the cooperating rehabilitation centers (clusters), i.e., all study participants in these facilities are assigned to the intervention condition. In the other half of clusters, the control condition is implemented. After nine months, the clusters cross so that the intervention condition will now be implemented in the previous “control clusters” and vice versa (Fig. 2). Which facilities enter the intervention or control phase first is determined in advance by randomization.

**Fig. 2 Fig2:**
[figure not shown]
Crossover design. Note: MR = medical rehabilitation

Participants in the intervention group (IG) and the control group (CG) will receive the usual recommendations for rehabilitation aftercare during their rehabilitation stay. Participants in the IG will also receive an invitation for the follow-up consultation with their GP, which is scheduled to take place four to eight weeks after completion of MR. Participants in the control group (CG) do not receive a follow-up consultation with their GP.

Given the small scale and effort of the intervention required on the part of the rehabilitation centers, we do not expect any carry-over effects and see no need to introduce a washout period before the change of conditions in the facilities [55].

The study staff will randomly assign the clusters using an online research tool (Research Randomizer; randomizer.org).

There will be no blinding of healthcare professionals in the rehabilitation centers or GPs, as knowledge of the status of study participants (intervention / control condition) is necessary for the provision of information and materials (rehabilitation centers) or the intervention (GPs). The study team will inform the rehabilitation centers of their respective allocation in written form so that they can organize study materials and procedures accordingly.

On the part of rehabilitation patients, study participants will be blinded with regard to group assignment (intervention/control condition). Due to the nature of the study, we do not expect that emergency unblinding will be necessary.

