A written patient communication aid will be developed to support patients in the follow-up consultation. Where appropriate and useful, it will reflect the content and structure of the GP consultation guide. The communication aid is intended to help patients reflect on the following topics: current state of health; perceived changes and improvements as a result of MR; achievement of rehabilitation goals; implementation of aftercare recommendations. It is designed to encourage patients to ask questions and express their preferences during the follow-up consultation based on the modified PACE framework [39, 40], and to clarify their health-related values [41, 42].

Intervention group participants will receive a written invitation to the follow-up consultation. In order to increase the commitment and attractiveness of the follow-up consultation, the invitation will be communicated as a ”Let’s talk about your health” voucher (including the patient communication aid). The specific distribution of the invitation and accompanying materials depends on when and by whom the follow-up recommendations are provided in the respective rehabilitation facilities, for example, during the final medical consultation. This will be clarified in the first study phase.

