### Study design and data collection

#### Rehabilitation patients

In the first phase of the study, we will collect qualitative data in interviews with MR patients to evaluate comprehensibility and user-friendliness of the patient communication aid, which is intended to support study participants during the follow-up consultation with their GP. Participants will be presented with the draft version of the communication aid. In all sections, respondents will be asked to explain to what extent the individual items are comprehensible and whether there are any suggestions for rewording or other modifications. The procedure is based on the cognitive interview methodology and the “think aloud” method [43, 44].

In the second study phase, we will collect quantitative data (written questionnaires) in six inpatient rehabilitation centers in Northern Bavaria and neighboring regions. Questionnaire data will be collected longitudinally at three measurement points (T1: end of MR; T2: after follow-up consultation with GP (intervention group only; four to eight weeks after completion of MR); T3: four months after completion of MR).

The primary outcome is the self-reported utilization (initiation/continuation) of rehabilitation aftercare at T3 (four months post-rehabilitation). Self-reported work ability at T3 is assessed as a secondary outcome. We will collect additional variables to describe the sample and/or include them in moderator or predictive analyses. Table 1 summarizes the instruments used at each measurement point.

**Table 1 Tab1:** Instruments used in the study

Variable	Measure	T1 Completion of MR		T2 After follow-up consultation (IG only)		T3 4 months after completion of MR	
		IG	CG	IG	CG	IG	CG
Rehabilitation aftercare motivation, expectations	single items developed for this study	**X**	**X**				
Rehabilitation aftercare self-efficacy	single items developed for this study	**X**	**X**				
Rehabilitation aftercare recommendations by MR facility	single items developed for this study	**X**	**X**				
Evaluation of medical rehabilitation outcomes (subjective success of rehabilitation)	single items developed for this study	**X**	**X**				
Self-reported work ability	WAS [45, 46]	**X**	**X**				
Health-related quality of life	EQ-5D 5 L [47]	**X**	**X**				
Health literacy	HLS19-Q12-DE [48]	**X**	**X**				
Perceived communicative self-efficacy in patient-physician interactions	Single item developed for this study, based on Maly et al. [49]	**X**	**X**				

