Sociodemographic, socio-medical data	single items based on recommended sociodemographic indicators in rehabilitation research [50, 51]	**X**	**X**				
Rehabilitation aftercare motivation	single items developed for this study			**X**	**---**		
Rehabilitation aftercare self-efficacy	single items developed for this study			**X**	**---**		
Use of/participation in follow-up consultation	single items developed for this study			**X**	**---**		
Evaluation of follow-up consultation	single items developed for this study			**X**	**---**		
Implementation of aftercare recommendations by MR facility	single items developed for this study			**X**	**---**		
Evaluation of medical rehabilitation outcomes (subjective success of rehabilitation)	single items developed for this study			**X**	**---**		
Self-reported work ability	WAS [45, 46]			**X**	**---**		
Health-related quality of life	EQ-5D 5 L [47]			**X**	**---**		
Health literacy	HLS19-Q12-DE (51)			**X**	**---**		
Socio-medical data (return to work status)	single items based on recommended sociodemographic indicators in rehabilitation research [50, 51]			**X**	**---**		
Rehabilitation aftercare initiation/ continuation (primary outcome); reasons for non-use	single items developed for this study					**X**	**X**
Rehabilitation aftercare motivation	single items developed for this study					**X**	**X**
Rehabilitation aftercare self-efficacy	single items developed for this study					**X**	**X**
Evaluation of medical rehabilitation outcomes (subjective success of rehabilitation)	single items developed for this study					**X**	**X**
Self-reported work ability	WAS [45, 46]					**X**	**X**
Health-related quality of life	EQ-5D 5 L [47]					**X**	**X**
Health literacy	HLS19-Q12-DE [48]					**X**	**X**
Socio-medical data (return to work status)	single items based on recommended sociodemographic indicators in rehabilitation research [50, 51]					**X**	**X**

Note: MR = medical rehabilitation; IG = intervention group; CG = control group

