### Recruitment

In each cooperating rehabilitation center, a responsible person (“study coordinator”) will be appointed, who will be briefed by the research team and be provided with all important information, including inclusion and exclusion criteria, as well as materials for recruitment and data collection (study information, declaration of consent, questionnaires) within the facility. This person will be specifically responsible for contacting eligible patients and asking them to participate in the study, distributing (and collecting) all relevant documents after informed consent to participate in the study has been given, and providing and managing materials related to the intervention (information flyers/vouchers for the follow-up consultation) during the data collection period in which the respective facility is assigned to the intervention condition.

The rehabilitation center will hand out T1 questionnaires to study participants. To ensure anonymity, the respective rehabilitation centers will also mail T2 and T3 questionnaires to study participants (the latter can also be completed online). To simplify their return and to reduce the dropout rate, the envelopes for all questionnaires (T1, T2, T3) are prepaid. The rehabilitation facilities will receive a flat fee of €20 per study participant recruited for their recruitment efforts.

For practical reasons, we will recruit GPs via various channels:

First, the Bavarian Association of General Practitioners will inform GPs about the study (incl. eligibility for reimbursement of follow-up consultations) via the association’s newsletter and other resources, several times if necessary.

In addition to the rehabilitation discharge report, which is sent to the respective GP as standard, the cooperating rehabilitation centers will enclose an information sheet and other written materials that identify the respective patient as a study participant.

The sheet contains information about the study and the follow-up consultation. In particular, it includes a link to the project website, where GPs will complete the evaluation questionnaire after each follow-up consultation.

Study patients will also receive an “information package” containing the relevant study documents as well as information and materials for their GP. When making an appointment for the follow-up consultation, patients will be asked to present the materials to their GP and ask them to participate in the study.

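### Patients are called blinded although intervention patients hold the voucher and attend the consultation, and an intervention-only T2 questionnaire adds an aftercare prompt before the self-reported primary outcome

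*Protocol article*

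**What the plan says.** In the Randomization section (text after Fig. 2), the protocol article states two things about blinding. For staff and GPs: "There will be no blinding of healthcare professionals in the rehabilitation centers or GPs". For patients: "study participants will be blinded with regard to group assignment (intervention/control condition".

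The same section says "Participants in the IG will also receive an invitation for the follow-up consultation with their GP", and that controls have no such consultation. The Intervention section adds "Intervention group participants will receive a written invitation to the follow-up consultation", and explains that "the invitation will be communicated as a ”Let’s talk about your health” voucher (including the patient communication aid". Under Recruitment, "When making an appointment for the follow-up consultation, patients will be asked to present the materials to their GP" and to ask the GP to join the study.

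On measurement, the section on study design and data collection defines the second time point as "T2: after follow-up consultation with GP (intervention group only; four to eight weeks after completion of MR". Table 1 marks the control column at T2 as empty. The primary outcome is the patient's own report of starting or continuing aftercare at T3, on items written for this study.

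**The concern.** There are two separate problems.

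First, the blinding sentence is a positive claim that the article's own procedures contradict for at least one group. A reader who trusts it will assume that knowledge of the assigned condition cannot influence how patients answer the T3 aftercare questions. Patients who were invited to talk about aftercare with their own doctor may be more inclined to report having used it.

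Second, the consultation is the intervention and has to differ between the groups, but T2 is measurement and does not. Asking only one group about aftercare part-way through follow-up gives that group an additional reminder and an additional study contact. The comparison at T3 is then consultation plus questionnaire against neither, and the two cannot be pulled apart.

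**Working it through.** The plan gives no figure on this point, so the check is mainly a comparison of its statements.

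**1. Can an intervention patient be unaware of the assigned condition?** The patient receives a named voucher with a communication aid (Intervention), is asked to hand study materials to the GP and seek the GP's participation (Recruitment), and has a consultation of at least 20 minutes (Intervention). The Retention strategies section adds that recruitment will stress the consultation as an extra offer. A patient who has done all this knows that he or she is receiving the studied offer. For this group the blinding statement cannot be true.

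**2. Can a control patient be unaware?** Allocation is by facility and period, so everyone recruited in a centre during a period has the same condition (Randomization). A control could therefore be kept from knowing that a consultation is being tested. The article does not describe this, and the recruitment message just mentioned sits uneasily with it.

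**3. What does T2 add?** From Table 1, the aftercare-related rows are:

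| Row | T1 | T2 | T3 |
|---|---|---|---|
| Aftercare motivation | both groups | intervention only | both groups |
| Aftercare self-efficacy | both groups | intervention only | both groups |
| Recommendations received | both groups | not asked | not asked |
| Implementation of recommendations | not asked | intervention only | not asked |
| Initiation/continuation (primary) | not asked | not asked | both groups |

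Both groups are prompted equally at T1. Between T1 and T3 only the intervention group is prompted again. The implementation row is the one close in content to the primary outcome. T2 falls four to eight weeks after rehabilitation and T3 at four months (about 17 weeks), so the extra prompt comes 17 − 8 = 9 to 17 − 4 = 13 weeks before the outcome is reported, which leaves time for it to act.

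**4. How much would it take to matter?** This is an illustration, because no reporting error is given in the article. Inputs from the Sample size section: control use 30%, planned difference 10 percentage points. Assumption: true use is 30% in both groups, controls report correctly, and a share *f* of intervention non-users report use.

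- Reported rate in the intervention group = 0.30 + 0.70 × *f*
- Spurious difference = 0.70 × *f*
- *f* = 5%: 0.70 × 0.05 = 3.5 points
- *f* = 10%: 0.70 × 0.10 = 7 points
- Whole planned difference: *f* = 0.10 / 0.70 = 14.3%

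These values show the scale on which reporting differences would become material. They do not estimate what will happen.

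**The case against.** The strongest reply is that the sentence speaks of group assignment, not of treatment received. With whole facilities assigned by period, patients could know what they were given without knowing that there are two conditions. The patient information that would settle this is not available here. This stands as a possibility for controls. It does not rescue the claim for patients who hold the voucher and attend the consultation, and it has no bearing on T2.

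It is also fair that a voucher and consultation cannot be concealed, and that the article openly calls the outcome self-reported. Unblinded self-report is largely inherent in this trial. The fault lies in saying otherwise and in adding an avoidable asymmetry.

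A reader might infer several stronger points, which the documents do not support:

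- *That the primary result will be biased by some stated amount.* No size is given. For the effect of T2 on T3 response, even the direction is open.
- *That T2 asks the primary outcome early.* It does not. Motivation and self-efficacy are separate variables, and only the implementation row comes close.
- *That work ability, quality of life and health literacy at T2 are flawed for want of control values.* No between-group comparison at T2 is planned, and work ability is a secondary outcome at T3, where both groups are measured.
- *That contamination of controls goes unmeasured.* The row "Use of/participation in follow-up consultation" is intervention-only, but it concerns the study consultation, which controls are not offered. The wording of the T3 items is not shown, so what they ask about GP contact or named programmes is unknown. Ordinary GP contact is also part of the usual-care comparator.

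**Conclusion.** The point holds in two parts. The statement that patients are blinded is wrong for the intervention group and unexplained for controls, so the self-reported primary outcome is not protected by patient blinding. Independently of how blinding is read, the intervention-only T2 places aftercare questions before T3 in one group only, and any resulting change in behaviour, reporting or response would count as an effect of the consultation.

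The contradiction and the asymmetry rest on the article's text alone and are certain. The amount of bias is unknown; the figures of 3.5 to 7 points depend entirely on the assumed 5% to 10% misreporting. Both parts should be corrected. Neither requires a change to the design, the intervention or the sample size.

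**What to change.** 1. Replace the blinding sentence in Randomization with a statement that patients are not blinded to the intervention, and say what, if anything, is withheld from controls. State that the primary result will be interpreted as unblinded self-report. Cost: a text correction.

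2. Limit the intervention-only T2 to attendance at the consultation and to its content and rating. This keeps the patient-side information on delivery that the Discussion relies on. Ask the aftercare motivation, self-efficacy and implementation items at T3 in both groups. By Table 1, motivation and self-efficacy are already there, so only the implementation item has to be added. Cost: loss of mid-point scores in the intervention group that have no control comparator, and one further T3 item.

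An alternative is to mail controls a matching T2 without the consultation items. With equal groups that is about 669 / 2 ≈ 335 mailings plus data entry. It would equalise contact, but it would also prompt controls about aftercare and move them away from care as usual, so shortening T2 is the better choice.

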### Sample size

#### Rehabilitation patients

We expect an effect of the intervention on patients’ self-reported use of rehabilitation aftercare four months after they have completed MR (primary outcome). Specifically, we assume that more patients in the IG will use or continue to use aftercare services than patients in the CG. Since CG patients also receive follow-up recommendations from their MR facility, we expect a small effect in favor of the IG.

Utilization of the GPI aftercare programs (IRENA, other) is around 30% [3, 56], which can be used as a minimum approximation for the control condition. We assume an additional utilization rate of 10% as a result of the intervention, i.e. 40% in total. This estimate is exploratory and, given the lack of data, rather conservative.

To calculate the sample size for the cluster randomized crossover trial, we used the Shiny CRT Calculator program [57, 58]. Our estimate for the intra-cluster correlation (ICC) is based on results from a study using GPI routine data for various medical indications (*n* = 653,081) [59]. In this study, researchers developed a risk adjustment strategy to improve the use of return to work as a quality indicator for medical rehabilitation. The ICC for the rehabilitation department level (i.e. indications) averages 1.95% (0.0195).

For six cooperating facilities (clusters), a sample size of 29 participants per cluster (clinic) and time period (intervention/control phase; see Fig. 1) is calculated with a power of 0.8 to demonstrate a small intervention effect, i.e. 174 persons for both the intervention and control conditions (total *n* = 348).

We calculated an expected dropout of approximately 35% from T1 to T2. Due to a lack of data from comparable studies, we used willingness to participate in various medical rehabilitation or aftercare studies as a proxy for willingness to participate in the follow-up consultation [23, 60–68]. Willingness to participate in these studies ranged between 42% and 85% (mean: 67%). Moreover, presumably not all study participants will take part in the follow-up consultation and its use is also contingent upon the participation of the respective GPs. On this basis, we assume a realistic dropout rate of 35%.

From T2 to T3, a further dropout of approximately 20% can be assumed. Data from various rehabilitation studies with 3- or 6-month follow-ups show dropout rates ranging between 5% and 28%, with an average of 14% [30, 32, 65, 69–76]. A conservative estimate is therefore a dropout of 20%. This increases the required sample size to a total of *N* = 669 individuals (T1) (T2: *n* = 435 due to a dropout rate of 35%).

The aim of the interviews with rehabilitation patients to evaluate the communication aid for patients (Phase 1) is to cover all indications included in the cooperating rehabilitation centers (orthopedics, endocrinology/diabetology, cardiology). We plan to recruit two to three individuals per indication. The objective of the interviews has a defined focus, the sample can be considered specific to the study context, and the interviews are characterized by a high degree of interactivity and dialogue. According to Malterud et al. [77], it can therefore be assumed that the proposed number of participants is sufficient to obtain the desired information for evaluating the communication aid. In addition, this limits the effort required to conduct the interviews (recruiting participants by clinic staff, finding time slots for participants outside their therapy schedules, organizing and securing rooms in the rehabilitation center, travel arrangements for project staff).

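### The stated power of 0.8 does not follow from the protocol's own inputs: 348 analysed patients give about 51%, and 80% would need about twice as many

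*Protocol article*

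**What the plan says.** The protocol article, Sample size (Rehabilitation patients), gives the inputs and the result in one place.

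- Control rate: "Utilization of the GPI aftercare programs (IRENA, other) is around 30" percent, "which can be used as a minimum approximation for the control condition".
- Effect: "We assume an additional utilization rate of 10% as a result of the intervention, i.e. 40% in total".
- Correlation: "The ICC for the rehabilitation department level (i.e. indications) averages 1.95% (0.0195"). It is taken from a study of return to work, and it is the only correlation figure given.
- Result: "For six cooperating facilities (clusters), a sample size of 29 participants per cluster (clinic) and time period" "is calculated with a power of 0.8 to demonstrate a small intervention effect", "i.e. 174 persons for both the intervention and control conditions", with a total of 348.

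The Randomization section fixes the geometry: "during the first nine months of data collection, the intervention will be carried out in half of the cooperating rehabilitation centers (clusters"), after which the conditions swap. That is three clinics per sequence and two nine-month periods.

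The section does not state alpha, sidedness, a between-period correlation or a reference distribution.

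**The concern.** For a simple comparison of 30% with 40% at two-sided 5% and 80% power, about 353 patients per condition are needed under individual randomization. A two-period cluster crossover with one ICC saves almost nothing on that: its design effect is 1 − 0.0195 = 0.9805. A plan with 174 per condition therefore has about half the patients that its own assumptions call for.

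The 348 carries the later figures: 435 at T2, 669 at T1 and the estimate of 77 GPs. A reader who believes the trial has 80% power for a 10-point gain would take a null result as evidence against the consultation. At about 51%, a true 10-point gain would be missed about half the time.

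**Working it through.** **Inputs from the protocol.** p0 = 0.30, p1 = 0.40, ICC = 0.0195, six clinics, m = 29 per clinic and period (6 × 29 = 174 per condition).

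**Assumptions.** Alpha is two-sided 5% unless said otherwise. CAC is the between-period autocorrelation of clinic levels; 1 means perfectly stable levels.

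**Formulas.**
- Design effect: DE = 1 + (m − 1)·ICC − m·ICC·CAC
- SE² = [p0(1 − p0) + p1(1 − p1)]·DE/(6m)
- Normal reference: power = Φ(0.10/SE − 1.96). With few clusters: noncentral t with the stated degrees of freedom.

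**1. Attempt to reproduce 0.8, most favourable case (CAC = 1).** DE = 1 + 28 × 0.0195 − 29 × 0.0195 = 0.9805. SE² = (0.21 + 0.24) × 0.9805/174, so SE = 0.0504. 0.10/0.0504 = 1.986, and Φ(1.986 − 1.960) = 0.51.

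Other significance levels: one-sided 5% gives 63%, one-sided 10% gives 76%. Other ICCs at CAC = 1: 0.01, 0.05 and 0.10 give 50.7%, 52.3% and 54.5%. None of these settings reaches 80%.

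**2. Detectable difference at m = 29 (CAC = 1, normal).** Against a 30% control rate, power is 79% for 14 points and 82% for 14.5 points, so 80% is reached at about 14 points.

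**3. What the stated inputs need.** Per condition: (1.960 + 0.842)² × 0.45/0.01 × 0.9805 ≈ 346. Dividing by six clinics gives 57.7, so 58 per clinic and period, or 58 × 12 = 696 analysed. Power at 58 is 80.2%.

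**4. Two ways in which 29 could arise.**
- Twelve clinics (six per sequence), m = 29, CAC = 1, normal reference: power 80.2%.
- Six clinics and a standardized effect of 0.3: 2 × 7.85/0.09 × 0.9805/6 = 28.5, so 29. The stated 30% vs 40% corresponds to about 0.21 (arcsine scale).

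**5. Dropout steps.** 348/0.80 = 435 and 435/0.65 = 669. These are right; the error lies in the 348.

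**6. Sensitivity at 58 per clinic and period (CAC and degrees of freedom are assumptions).** The 4 df come from 12 clinic-period means less 6 for clinics, 1 for period and 1 for treatment.

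| CAC | DE | Normal | t, 10 df | t, 4 df |
|---|---|---|---|---|
| 1.0 | 0.981 | 80% | 72% | 57% |
| 0.9 | 1.094 | 76% | 67% | 52% |
| 0.8 | 1.207 | 72% | 63% | 49% |
| 0.6 | 1.433 | 64% | 55% | 43% |

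**7. Where the ICC matters.** At 58 and CAC = 1, raising the ICC from 0.0195 to 0.05 moves power from 80.2% to 81.4%. At CAC = 0.8 the same change takes it from 72% to 61%.

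**8. Control rate.** The 30% is called a minimum. With the same 10-point gain from a control rate of 40–50%, power (CAC = 1, normal) is 47–48% at 29 and 76–77% at 58.

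**The case against.** The best defence is that an article need not print every calculator setting, and that the between-period correlation, the reference distribution and the small-sample method may stand in a fuller protocol or analysis plan. This holds for the sensitivity in step 6: silence on these settings is not an error, and the size of the further loss rests on assumed values. It does not rescue the 0.8. That figure is printed with its inputs, and it fails under the settings most favourable to the plan.

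Three stronger readings are tempting, and the document does not support them.

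- A reader might infer that the borrowed return-to-work ICC, or the missing allowance for clinic-by-period variation and few clusters, explains the fall from 80% to 51%. It does not. With stable clinic levels the ICC has almost no effect, and the 51% already uses a normal reference. The fall is the factor of two in the count. Borrowing an openly sourced ICC is ordinary practice.
- A reader might infer that six clinics were entered per sequence. This fits, but so does a standardized effect near 0.3, and the text speaks of a small effect. The origin is undetermined.
- A reader might take the 4-df figures as the trial's true power. Four df is the harshest choice. The penalty depends on the analysis and largely disappears if clinic-by-period variance is truly zero and patient-level degrees of freedom apply.

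**Conclusion.** The stated power is wrong as written. With six clinics, two periods and 29 patients each, 30% against 40% and ICC 0.0195, power is about 51% at two-sided 5%, and the detectable difference is about 14 points rather than 10. Alpha had to be assumed, but one-sided 5% (63%) and one-sided 10% (76%) also fall short of 80%. On its own inputs the plan needs about 58 per clinic and period, or 696 analysed.

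Doubling the count would not by itself secure 80%, since that also needs perfectly stable clinic levels and a normal reference. The direction of the further loss is certain. Its size is not: 64–76% (normal) or 43–52% (4 df) for an assumed autocorrelation of 0.6 to 0.9, and 72% (10 df) or 57% (4 df) at an autocorrelation of 1. The choice of ICC matters only when the autocorrelation is below 1.

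This must be fixed, because the trial's size and the reading of a null result rest on the figure.

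**What to change.** Re-run the calculation with three clinics per sequence and the stated 30% vs 40%, and state alpha and sidedness. Replace the 0.8 with the power and detectable difference that 348 analysed patients give. Show both over a labelled range of between-period autocorrelation (for example 0.6–1.0) and ICC (for example 0.02–0.05), with a small-sample reference suited to six clinics that matches the primary analysis.

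Say plainly that the plan's own inputs would need about 58 per clinic and period for 80% even in the best case. Under the protocol's dropout rates that is 696/0.80 = 870 at T2 and 870/0.65 ≈ 1,339 at T1, against 669 planned.

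Restating costs a recalculation and a less favourable stated power. It needs no extra patients or clinics, but it also does not raise the power. Whether to enlarge the trial or accept the lower power is then an open decision for the study team.

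### The stated 29 patients per clinic and period (348 in total) gives at most about 51% power for 30% versus 40%, not 80%

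*Protocol article*

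**What the plan says.** In the protocol article, Methods, Sample size, Rehabilitation patients, the control rate is set at about 30%, a figure "which can be used as a minimum approximation for the control condition". The gain is then fixed: "We assume an additional utilization rate of 10% as a result of the intervention, i.e. 40% in total". The ICC is 0.0195, taken from a routine-data study of return to work. For six clinics, the result reads: "a sample size of 29 participants per cluster (clinic) and time period (intervention/control phase; see Fig. 1) is calculated with a power of 0.8", for what the article terms a small effect. The text converts it to "174 persons for both the intervention and control conditions", with a total of 348.

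The section then adds losses of 35% (T1 to T2) and 20% (T2 to T3). "This increases the required sample size to a total of" 669 at T1, with 435 at T2. The paragraph on general practitioners also takes 348 as its base.

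Under Randomization, each of the six clinics spends one nine-month period in each condition. Neither alpha nor the between-period correlation is given in the article.

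**The concern.** A 10-point difference around 35% usually needs roughly 350 patients per arm under individual randomisation. A cluster crossover can remove the between-clinic variance, but that is only about 2% of the total when the ICC is 0.0195. The design therefore cannot halve the sample, yet 174 per condition is half the usual figure.

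At stake is the stated power for the primary outcome of a trial described as a superiority trial. If the true gain is the 10 points assumed, the trial as sized would miss it about half the time or more often.

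**Working it through.** **Inputs from the article.** 30% and 40%; ICC 0.0195; six clinics, two periods, different patients in each period; m = 29 per clinic-period; power 0.8.

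**Inputs assumed.** Two-sided alpha of 0.05, with alternatives shown. The cluster autocorrelation (CAC, the between-period correlation divided by the ICC) is varied from 1, the most favourable value, downwards.

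**1. The article's own arithmetic.** 6 × 29 = 174 per condition; 12 × 29 = 348 in total; 348/0.80 = 435; 435/0.65 = 669.2. These steps are consistent, and they show that 348 is used as the total analysed.

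**2. Individually randomised requirement.** n per arm = (1.960 + 0.8416)² × (0.30×0.70 + 0.40×0.60)/0.10² = 353.2. The pooled-variance formula gives 356.

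**3. Design effect.** DE = 1 + (m − 1)×ICC − m×CAC×ICC. At CAC = 1 this is 1 − 0.0195 = 0.9805, the lowest value it can take.

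**4. Requirement with six clinics.** 353.2 × 0.9805 = 346.3 per condition. Divided by 6 this is 57.7, so 58 per clinic-period: 348 per condition and 696 analysed. The pooled formula gives 59. At CAC = 0.8 it is 75 per clinic-period: DE = 1 + 74×0.0195 − 75×0.8×0.0195 = 1.273, and 353.2 × 1.273 = 449.6, so 450 per condition and 900 analysed.

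**5. Power at 29 per clinic-period.** z = 0.10/√(0.45/174 × DE); power = Φ(z − 1.960).

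| CAC | DE | z | Power, two-sided 5% |
|---|---|---|---|
| 1 | 0.9805 | 1.986 | 0.51 |
| 0.8 | 1.0936 | 1.880 | 0.47 |
| 0.5 | 1.2632 | 1.750 | 0.42 |
| 0 | 1.5460 | 1.581 | 0.35 |

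The pooled formula gives 0.506 at CAC = 1. A simulation of six clinics and two periods gave 0.508 at 29 per clinic-period and 0.803 at 58.

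**6. Attempts to recover 0.8 with 174 per condition, all at CAC = 1.**
- One-sided 5%: 0.63.
- Two-sided alpha of 0.25: 0.80.
- A small effect read as a standardised difference of 0.2: z = 0.2/√(2/174 × 0.9805) = 1.884, power 0.47.
- t reference distribution with 4 to 10 degrees of freedom, as few clusters might require: 0.33 to 0.44.

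**7. Detectable difference.** At CAC = 1, two-sided 5% and 80% power, 174 per condition detects 30% versus about 44.3%, roughly 14 points. A lower CAC makes it larger.

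**8. Where 29 does fit.** 346.3/12 = 28.9. With twelve clinics, 29 per clinic-period gives 348 per condition, z = 0.10/√(0.45/348 × 0.9805) = 2.808 and power Φ(0.848) = 0.80.

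**The case against.** The best defence is that the article is condensed: alpha, sidedness and between-period correlation may be set out elsewhere, and the calculator's inputs are not shown. That stands as a caution, and I treat those values as assumptions. It does not rescue the figure. CAC = 1 is already the most favourable value, and a one-sided 5% test still reaches only 63%. Analysis of covariance is planned, but covariates would have to explain about half of the outcome variance (1 − 174/346.3 = 0.50), and the article claims no such gain.

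It might be said that 348 was meant per condition. The text excludes this: it gives 174 per condition, calls 348 the total, and inflates it as the total.

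Some stronger readings are tempting but not supported:
- **A known cause.** The match with twelve clinics suggests that six clusters were entered per sequence rather than in all. That is possible but not shown, and the numerical error does not depend on it.
- **A false claim of caution.** A reader might attack "This estimate is exploratory and, given the lack of data, rather conservative" because the 30% control rate is a floor. The sentence directly follows the assumed 10-point gain and most naturally describes that gain. A higher control rate also barely moves power: with 45% in the control group it is about 47%.
- **Cover from the dropout allowance.** One could count patients who skip the consultation but return T3. The article applies the 35% loss to the whole sample, so it offers no such margin.

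The article calls the effect estimate exploratory. That tempers the consequence, but it does not make the stated power correct.

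**Conclusion.** The stated power is wrong. For 30% versus 40%, ICC 0.0195 and six clinics with 29 per clinic-period, power is at most about 51% on a two-sided 5% test, and less if the between-period correlation is below the ICC. No conventional setting that I tried reaches 80%. The conclusion rests on two quantities the article does not give. For alpha I used the conventional value and showed how far it would have to move. For the between-period correlation I used the value that most favours the protocol.

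The figures of 58 per clinic-period, 348 per condition and 696 analysed are best-case minima, not a recommended target. The totals of 435 and 669 are correct as dropout arithmetic but start from a number that does not deliver the stated power.

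**What to change.** Re-run the calculation with six clinics in total, three per sequence. For 348 analysed, replace the power of 0.8 with the value obtained (at most about 51%) and give the detectable difference (at least about 14 points), naming the alpha and between-period correlation used. If the 80% requirement is mentioned, label 58 per clinic-period and 696 analysed as best-case minima, rising to about 75 and 900 at a correlation ratio of 0.8.

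Then treat 435 and 669 in one of two ways. Either re-caption them as the numbers needed to reach 348 analysed at the restated power, or recompute them. At the best-case minimum the article's own loss rates give 696/0.80 = 870 at T2 and 870/0.65 = about 1,339 at T1.

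The cost is one re-run of the calculator and a correction to the sample size text. The stated power becomes less favourable. No additional patients are needed unless the sponsor chooses to keep the 80% target.
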